#### Outcomes for MIMICH II

Primary infant outcome: Difference in the delta (birth to visit 2) weight SD score between infants following maternal treatment with or without metformin

Infant secondary outcomes:Metabolic health indices including biochemical (insulin, glucose, lipid profile, leptin, adiponectin)Anthropometric measurements (crown-rump, crown-heel lengths; weight; arm, thigh, head, abdominal circumferences; biceps, triceps, subscapular skinfold thicknesses) expressed as z-scores using WHO charts where applicableCardiac measurements including systolic and diastolic blood pressure and echocardiogram (left ventricular dimensions, diastolic function and systolic function)Transcriptomics and metabolomics are collected from infant and mother and differentially expressed genes and metabolites will be determined between metformin-exposed and non-exposed infants

Maternal secondary outcomes: Postnatal weight change (from booking to late pregnancy), adiposity (waist:hip ratio, biceps, triceps, subscapular skinfold thicknesses), cardiometabolic health measurements (insulin resistance, lipids, hsCRP, inflammatory cytokines, BP)

#### Adverse events

Adverse event recorded (number of women and number of adverse events) during treatment only. All AEs and SAEs identified will be recorded in the trial database and will be reviewed and signed by the PI. The trial sponsor will also be made aware of any SAEs that occur on trial and will be sent copies of the completed SAE forms.

As postnatal follow-up visits will not require treatment to be taken, any adverse events occurring during this time will not be recorded in the trial database.

If any abnormality is found in the bloods, blood pressure or echocardiograms at any point during active treatment or postnatal follow-up, this will be explained to the participant and we will inform their GP or refer to the appropriate clinical team depending on the clinical significance of the finding.

### Participant timeline {13}

The participant timeline for active treatment is presented in Fig. 1 and Table 1. As MIMICH is a pragmatic, phase III trial to refine the provision of routine antenatal care, no additional visits are required outside of normal care.

**Fig. 1 Fig1:**
[figure not shown]
Timeline of protocol for MIMICH participants

**Table 1 Tab1:** Schedule of visits and trial procedures for MIMICH

Procedures	Participant identification antenatal clinics	Baseline visit	Intervention period (study visits every 4 ± 2 weeks)	Fasting visit (30–34 weeks ± 2 weeks)	At/after birth
Routine antenatal visit	x	x	x	x	
Eligibility check	x	x			
Written informed consent		x			
Randomisation		x			
Collection of baseline characteristics (demographics, obstetric and medical history, medication)		x			
Confirmation of willingness to continue intervention			x	x	
Study visits every 4 ± 2 weeks (including ultrasound scan, BP, weight)		x	x	x	
Skinfold measurements		x		x	
Adherence with treatment: dose of insulin/metformin and self-reported number of missed doses in previous 7 days		x	x	x	x
Summary of glycaemic control and number episodes of hypoglycaemia (preceding 7 days)		x	x	x	x
Fasting blood samples (30–34 weeks only)				x	
Acceptability questionnaire completion [hard copy]				x	
Review of pregnancy complications/events			x	x	x
Research blood samples		x	x	x	x
Safety reporting			x	x	x
Pregnancy outcome/case note review					x
Collection of placenta and cord blood					x
Measurement of infant (within 5 days of birth)					x

Figure 2 and Table 2 depict the timelines for postnatal follow-up. As MIMICH II is concerned with postnatal care, all study visits will fall outside of routine care.

**Fig. 2 Fig2:**
[figure not shown]
Timeline of protocol for MIMICH II participants

**Table 2 Tab2:** Schedule of visits and trial procedures for MIMICH II

Procedure	MIMICH study visit	Birth	3–6 months postnatal visit	12 months postnatal visit
Consent	X			
Collection of maternal and neonatal outcome data		X		
Collection of clinical measurements			X	X
Maternal fasting blood sample			X	X
Infant fasting blood sample				X
Completion of study questionnaire			X	
Confirmation of willingness to continue			X	
Confirmation of additional complications				X
Confirmation of infant feeding type and age at weaning				X
Infant echocardiogram			X	X
Infant blood pressure				X

### Sample size considerations {14}

The primary outcome is a change in foetal growth velocity in the third trimester. Our group has pioneered the use of volumetric ultrasound techniques to improve the detection of foetal growth abnormalities [47, 48]. Previous studies investigating hypoglycaemic agents in pregnancy have used birthweight as the primary outcome, which provides only a crude estimate of foetal growth. In pregnancies where there are conflicting exposures influencing foetal growth and placental function (e.g. hypertension and hyperglycaemia), absolute birthweight is not sufficient to detect subtle, but clinically significant changes in foetal growth and placental function. To address this limitation, in this study, longitudinal measures of foetal growth will be used to quantify the deviation in foetal growth in the third trimester. This will be derived from the delta z-score in estimated foetal weight (using the modified EFW TVol formula [44]) over the third trimester using WHO foetal growth charts [43]. This will provide a more sensitive assessment of the effect of metformin on foetal growth than birthweight alone; the use of a continuous measure as a primary outcome also makes the study more efficient as it requires a smaller sample size. In order to verify the primary outcome, the eCRF will capture the TVol measurement and the EFW at each scan as well as recording the 2nd trimester and 3rd trimester deviation scores. The source data (scan report) will verify the 2D biometry.

In a comparison of women with type 2 diabetes treated with metformin recruited to the VELOCITY study, the mean delta z-score between the second trimester and birth was − 0.51 (SD 1.1) for women with a placental disease risk factor (*n* = 34) and 0.30 (SD 0.9) in women without a risk factor (*n* = 45). A sample size of 190 women (95 in each group) will provide 80% power to detect a clinically significant difference in delta z-scores of 0.41 (SD 1.0) between the treatment groups; this difference would reflect a rightward shift in the birthweight distribution in women in whom metformin was withheld to a mean of − 0.1.

An adjusted analysis of the effect of the intervention (withholding metformin) on foetal growth will include covariates (mean daily glucose, time in target) which are known to influence foetal growth to improve the precision of the treatment effect as appropriate. Change in foetal weight z-score provides a continuous measure of late pregnancy growth trajectory derived from early foetal biometry and 3D volumetric measurements and therefore the foetus is its own control. Importantly, this removes the need to adjust for infant sex. Furthermore, as the measurement of foetal weight z-scores using 3D foetal thigh volumes, and therefore calculation of delta z-scores is done after birth, the risk of bias is minimised. In the MiTy trial [11], a comparison of metformin vs no metformin in unselected women with type 2 diabetes, the difference in birthweight z-score was − 0.28 (− 0.45 to − 0.10).

Recruitment figures have been based on attendances to the Manchester Antenatal Vascular Service (MAViS) clinic, which provides care for women with cardiometabolic disease, and the diabetes service across Manchester Foundation Trust. Allowing for the fact that the proposed study will draw from a population of 16,500 pregnancies per annum, eligible women will include those with type 2 diabetes (*n* ≈ 108) and women who develop GDM with additional risk factors for placental disease (*n* ≈ 420). A recruitment rate of 50% would yield an available cohort of approximately 225 women (10% dropout) over a 36-month time frame. Based on figures from the MAViS cohort, 20% would be expected to develop a small for gestational age (SGA < 10th centile) and 12–18% pre-eclampsia.

The primary outcome for the postnatal follow-up study will be weight gain trajectory, determined as change in weight z-score, between birth and 12 months of age. Assuming a population z-score weight gain of 0.08–0.12 (SD 0.9) [37, 38] at 3–6 and 12 months, *n* = 39 (*β* = 0.8) or *n* = 70 (*β* = 0.9) per group will be required to show a 0.5 difference in z-score between groups (retention 35–63%). Excessive infant weight gain (> 0.67 SD, representative of the width of each percentile band on standard growth charts (e.g. 2nd–9th, 9th–25th percentile [8]) in the first year of life is strongly associated with an adverse adult cardiometabolic risk profile [36, 37]. Previous studies have demonstrated significant differences in adult cardiometabolic indices between groups of infants with rapid vs slow weight gain in the first 3–6 months after birth [49] using data from 65 and 22 adults, respectively. A conservative 0.5 change in z-score between metformin-exposed and non-exposed infants (at each time point) will therefore represent a robust and important clinical difference. Covariates (maternal glycaemic control, infant feeding, birthweight z-score and infant height) likely to be associated with the primary outcome will be included in the adjusted analysis to improve the precision of the treatment effect as appropriate. This will be balanced against the loss of effective sample size through use of degrees of freedom following inclusion of covariates [50].

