### Intervention description {11a}

Standard diabetes care follows the recommendations in NICE guidance NG3: ‘Diabetes in pregnancy: management from preconception to the postnatal period’. Home blood glucose monitoring (HBGM) may be either intermittent capillary glucose measurement or continuous glucose monitoring (CGM). Glucose targets, as per NICE, are fasting, 5.3 mmol/L and 1 h post-prandial, 7.8 mmol/L. Metformin is commenced where these targets are not met with diet and lifestyle advice/modification (in line with NICE guidance and guided by dietitian referral). Metformin dose is titrated to maternal tolerance as well as glycaemic control, starting at 500 mg twice daily with meals, increased every 3–5 days up to a maximum of 2500 mg daily in divided doses. Insulin is introduced where glucose targets are not met having reached the maximum tolerated dose of metformin. Insulin prescription is tailored to individual glycaemic profile using a long-acting (detemir or isophane) or rapid-acting (aspart) insulin, in isolation or combination. Insulin dose changes will be recommended to participants at a minimum of 3-day intervals according to HBGM as per standard clinical care. Diabetes treatment is supervised by a team of specialist midwives, obstetricians and diabetologists.

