### Criteria for discontinuing or modifying allocated interventions {11b}

Usual clinical care will be provided (following local and NICE guidelines), and medication will be titrated to glucose levels; no trial-specific treatment modifications are planned. Stopping or switching diabetes treatments is a common part of usual clinical care in pregnancy, and in order to maintain safety, it is anticipated that some participants will need to take metformin in the intervention arm. In addition, some participants allocated to usual care will not be able to tolerate metformin. Failure to tolerate metformin (usual care arm) will not be reported as an adverse event unless related to a reportable serious adverse event. All modifications to treatment allocation will be documented and included as secondary outcomes. A participant can continue in the study after discontinuation of treatment.

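### The power calculation takes its reference mean from women with a placental risk factor but uses SD 1.0 rather than that group's 1.1; without adjustment, power at 190 women is about 72%, not 80%

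*Protocol article*

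**What the plan says.** All the planning inputs are in the protocol article, Sample size considerations {14}. An earlier study of metformin-treated women with type 2 diabetes supplies two sets of figures for the delta z-score from second trimester to birth:

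- with a placental risk factor: mean −0.51, n = 34, reported as "SD 1.1) for women with a placental disease risk factor";
- without a risk factor: mean 0.30, SD 0.9, n = 45.

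The design statement follows: 190 women, 95 per group, are said to give "80% power to detect a clinically significant difference in delta z-scores of 0.41 (SD 1.0) between the treatment groups". The section describes this difference as moving the mean to −0.1 when metformin is withheld. The recruitment target is about 225, with 10% dropout.

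Eligibility criteria {10} require every participant to have at least one placental risk factor. Statistical methods {20a} set the primary analysis as a linear regression of the delta z-score, adjusted for baseline z-score and the minimisation variables.

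**The concern.** The mean and the SD come from different populations. The target difference is anchored on the risk-factor group alone, since −0.51 + 0.41 = −0.10, the stated target mean. The SD is not that group's. It matches the value obtained by pooling with women whom the eligibility criteria exclude, and the section gives no reason for using it.

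The choice favours the design, because sample size rises with the square of the SD: (1.1/1.0)² = 1.21, or 21% more women for the same power. The Discussion describes the trial as powered for a robust comparison of growth velocity. If the 80% does not follow from the protocol's own pilot data, readers are given a better account of the trial's sensitivity than the document supports.

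**Working it through.** **Inputs.** Difference 0.41; SDs 1.1 (n = 34) and 0.9 (n = 45); 95 per group; target 225 with 10% dropout (Sample size considerations). Allocation 1:1 (Trial design). Alpha is not stated for the primary outcome; two-sided 0.05 is assumed.

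**1. Reproduce the stated figure.** Two-sample t-test, standard error = SD × √(2/n).
- SD 1.0, n = 95: SE = 1.0 × √(2/95) = 0.145; 0.41/0.145 = 2.83; power 80.3%.
- Solving for 80% gives 94.4, so 95 per group. The stated figure is reproduced.
- One-sided 0.05 would need only 74 per group, so two-sided 0.05 is the reading that fits.

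**2. Where 1.0 may come from.** Pooled SD = √[(33 × 1.21 + 44 × 0.81)/77] = √(75.57/77) = 0.99. The protocol does not say this is its source; the values agree to rounding.

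**3. Power with the risk-factor group's SD, unadjusted.** 225 × 0.9 = 202.5, taken as 202 evaluable (101 per group).

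| SD | Evaluable | Power | Difference detectable at 80% |
|---|---|---|---|
| 1.0 | 190 | 80.3% | 0.41 |
| 1.1 | 190 | 72.4% | 0.45 |
| 1.1 | 202 | 75.0% | 0.44 |

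At SD 1.1, 80% power needs 114 per group, or 228 evaluable. That is above the recruitment target of 225 before any dropout, so the dropout margin does not close the gap. The normal approximation gives 72.9% and 75.5% in place of 72.4% and 75.0%.

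**4. What adjustment could recover.** Residual SD = 1.1 × √(1 − R²), where R is the multiple correlation of the adjustment covariates with the delta z-score.
- To reach 1.0: R = √[1 − (1/1.1)²] = 0.42, or R² of about 0.17.
- Power at 190 (normal approximation): R = 0.2 gives 75%, 0.3 gives 77%, 0.4 gives 80%, 0.5 gives 84%.
- At 202 evaluable, 80% power needs a residual SD of about 1.035, so R = √[1 − (1.035/1.1)²] = 0.34.

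**5. Precision of the 1.1.** The 95% interval for an SD of 1.1 on 33 degrees of freedom is 1.1 × √(33/χ²), about 0.89 to 1.45. It contains 1.0, and it also contains values well above 1.1.

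**The case against.** The best defence is that the planned analysis is not an unadjusted t-test. The delta is birthweight z-score minus baseline z-score, so it will normally correlate negatively with baseline, and an R² of 0.17 is a modest requirement. As an illustration, assume baseline and birthweight z-scores each have SD 1.0. A delta SD of 1.1 then implies 1.21 = 2 − 2r, so r = 0.395; the residual SD is √(1 − 0.395²) = 0.92 and power at 190 is 86%. Letting the baseline SD run from 0.9 to 1.1 and the birthweight SD from 1.0 to 1.2 gives residual SDs of 0.89 to 1.05 and power of 76% to 88%. These SDs are assumptions, not protocol figures, but they show that 80% may well be attainable.

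This stands as a reason not to call the trial underpowered. It does not rescue the statement as written. The section does mention adjustment for mean daily glucose and time in target to improve precision, but it does not present 1.0 as a residual SD and gives no correlation. It also lists 1.0 after two raw SDs, without marking any change of meaning.

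A second defence is that 1.1 is not the SD of the enrolled population. It comes from 34 women with type 2 diabetes, all on metformin, whereas the trial also enrols women with gestational diabetes and withholds metformin in one arm. That is correct, and 1.0 is compatible with those data. Still, 1.1 is the only SD the document gives for women with a risk factor, and the design relies on the same 34 women for its mean. Imprecision is a reason to show the sensitivity, not to take the lower value without comment.

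A reader might also infer that power is lower still because treatment contrast will be diluted: in usual care "Metformin is commenced where these targets are not met with diet and lifestyle advice/modification", and "it is anticipated that some participants will need to take metformin in the intervention arm". The documents do not support putting a figure on that here. The 0.41 is presented as a target difference between the randomised groups, not as a metformin-versus-none effect that then has to be discounted, and no cross-over rate is given.

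**Conclusion.** The concern holds as an unjustified input, not as an arithmetic error: 0.41 with SD 1.0 and 95 per group does give 80%. With the SD of the group that supplies the mean, unadjusted power is about 72% at 190 evaluable women and about 75% at 202, with detectable differences of 0.45 and 0.44. These figures assume two-sided 5% and SD 1.1 in both arms.

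A reader might go further and conclude that the trial has only 72% power. The document does not show that. The 72% belongs to an unadjusted comparison and rests on an SD estimated from 34 women. The adjusted primary model could reach 80% if the multiple correlation is about 0.42 or more (about 0.34 at 202 evaluable). What can be said is that the stated 80% does not follow from the pilot data beside it, and that the assumption needed to recover it is missing.

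**What to change.** In Sample size considerations {14}, do one of the following:

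- restate the power at SD 1.1 without adjustment as about 72% with 190 evaluable women and about 75% with 202 (detectable differences 0.45 and 0.44); or
- keep SD 1.0, say that it is a residual SD after the planned adjustment, and give the assumed multiple correlation with the delta z-score (about 0.42 if the raw SD is 1.1).

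In either case, state the alpha and sidedness, and note that the 1.1 comes from 34 metformin-treated women with type 2 diabetes and is therefore imprecise for the mixed population enrolled.

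The cost is two or three sentences and, under the first option, a less favourable power figure. Recruitment and the primary analysis do not change.

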### Outcomes {12}

#### MIMICH

Outcomes will be recorded in the electronic case report form, hosted on REDCap. Outcomes will be collected from baseline to maternal discharge post-birth. Neonatal outcomes will be recorded up to 28 days after birth.

Primary outcome:

Third trimester foetal growth velocity, assessed by change in foetal growth z-score between 20 and 29 weeks’ gestation (average) and birth.

At each scan, the estimated foetal weight (EFW) in grams will be calculated using 2D biometry and fractional thigh volume (TVol) measurements using a standard formula [44] and converted to a z-score [43]. The delta change in z-score between the average z-score of scans performed between 20 and 29 weeks and the birthweight z-score will be calculated.

Secondary outcomes:

During pregnancy, secondary outcomes will be reported as per standard for pregnancy intervention trials. Secondary foetal growth and birthweight analyses will be assessed according to treatment group in line with the primary outcome analysis. Outcomes relating to blood glucose control (as an indicator of treatment effect) will similarly be compared between groups, as will blood pressure and hypertensive complications. Reporting and analysis of secondary outcomes will be described in full in the statistical analysis plan; to avoid issues of multiple testing, not all secondary outcomes will be compared between treatment groups. Secondary outcomes will be assessed using adjusted linear regression for continuous outcomes and chi-squared for categorical outcomes; *p* values > 0.01 and < 0.05 will be interpreted with caution. Where appropriate, outcomes will be presented with a treatment effect and confidence intervals; other outcomes will be presented with summary statistics only.

Prespecified secondary outcomes:

Adherence/acceptability:Number of missed doses—calculated as an average over pregnancy from the number of missed doses reported in the 7 days prior to each study visit (adjusted for number of study visits)Number of women unable to comply with allocated treatment (cross over)Undesirable effects of allocated treatment (number of women reporting undesirable effects associated with metformin and/or insulin/number of women receiving metformin or insulin treatment)Treatment satisfaction with allocated medication regime (questionnaire)Acceptability of allocated medication regime (questionnaire)

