## Statistical methods

### Statistical methods for primary and secondary outcomes {20a}

The statistical analysis will be conducted according to the approved statistical analysis plan. Baseline characteristics of the trial population will be presented as mean and standard deviation (or median and interquartile range as appropriate). The main analysis will be an intention to treat analysis for the primary and secondary outcomes. For the primary outcome, the average z-score for estimated foetal weight (calculated using the modified EFW formula which incorporates TVol [44]) performed between 20 and 29 weeks will be calculated. This will be 1–3 scans per woman. The delta between the birthweight z-score and the 20–29-week z-score will be calculated. Delta z-scores will be compared between treatment groups using linear regression models adjusted for baseline z-score and minimisation variables (these will be confirmed in the final statistical analysis plan). All secondary outcomes will be reported as described in the outcomes section and analysed in accordance with the prespecified statistical analysis plan.

Missing data for baseline prognostic factors are not anticipated since they must be recorded to allocate treatment. All observed outcome data will be included in the analyses. As this is an exploratory study, we will focus on reporting the amount of missing data. We will report the number (%) of participants withdrawing fully from the trial and lost to follow-up by treatment arm. Reasons for missingness may be important, and these will be tabulated by treatment arm and documented as far as possible. Main analyses will be performed using STATA (StataCorp, College Station, TX, USA).

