### Methods for additional analyses (e.g. subgroup analyses) {20b}

Planned subgroup analyses on the primary outcome will investigate interactions between treatment effects and minimisation factors, with separate estimates and CIs reported for these subgroups of participants. In order to explore potential mechanism of action, exploratory analyses will estimate the effect of treatment received on the foetal growth outcomes.

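### The adjusted analysis described in the sample size section conditions on mean daily glucose and time in target, which the protocol elsewhere treats as outcomes of treatment, so as written it does not give a more precise treatment effect

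*Protocol article*

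**What the plan says.** Four parts of the protocol article bear on this.

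- **Sample size considerations {14}** announces "An adjusted analysis of the effect of the intervention (withholding metformin) on foetal growth" and says that it "will include covariates (mean daily glucose, time in target) which are known to influence foetal growth to improve the precision of the treatment effect", followed by the qualifier that this is done as appropriate. It gives no time of measurement for the two covariates and does not call the analysis supportive, mechanistic or exploratory.
- **Outcomes {12}, MIMICH** says of the glycaemic measures: "Outcomes relating to blood glucose control (as an indicator of treatment effect) will similarly be compared between groups". The list of standard secondary maternal outcomes then names mean daily glucose and percentage time in target, taken from home or continuous monitoring at every study visit and summarised by trimester.
- **Statistical methods {20a}** sets the primary comparison: "The main analysis will be an intention to treat analysis for the primary and secondary outcomes", and "Delta z-scores will be compared between treatment groups using linear regression models adjusted for baseline z-score and minimisation variables". There is no glucose term. The section leaves confirmation of these variables to the final SAP.
- **Additional analyses {20b}** has a separate place for questions of mechanism: "exploratory analyses will estimate the effect of treatment received on the foetal growth outcomes".

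**The concern.** Adjusting for a covariate improves the precision of a randomised comparison without changing its target only if treatment cannot have altered that covariate. Here treatment can. Metformin is given to lower glucose, and in both arms "medication will be titrated to glucose levels" throughout follow-up. The sample size section itself gives the influence of glycaemia on foetal growth as the reason for including it. A variable that treatment may shift and that in turn affects the outcome lies on the causal path.

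Conditioning on it has two consequences. First, the part of the effect that runs through glucose is removed, so the coefficient no longer answers whether withholding metformin affects growth. Second, anything that drives both glycaemia and growth and is not in the model, diet for example, becomes a source of confounding even though treatment was randomised.

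At stake is a second estimate of the trial's main contrast, presented as the more precise one while answering a different question. The article does not say how it relates to the model in the statistical methods section. If the two disagree, a reader has no stated rule for which to believe.

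**Working it through.** **1. The plan's own figure.** Inputs from Sample size considerations: difference 0.41, SD 1.0, 95 per group, 80% power. Two-sided alpha of 0.05 is assumed, since the article states none for the primary test.

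- n per group = 2(1.960 + 0.842)² × 1.0² / 0.41² = 93.4, so 94 per group or 188 in total, against 190 stated.
- Power with 95 per group: SE = √(2/95) = 0.1451; 0.41/0.1451 − 1.960 = 0.866; power 0.81.

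The stated size reproduces, and it involves no glucose adjustment.

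**2. Status of the two covariates.** Set side by side, the Outcomes section treats mean daily glucose and time in target as results of treatment, and the sample size section uses measures of the same names as covariates. Table 1 also marks a glycaemic summary at the baseline visit, and Implementation {16c} says allocation is released only after baseline measurements are complete. A pre-randomisation value therefore exists, but the sample size section does not say that this is the one to be used.

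**3. What the glucose-adjusted coefficient estimates.** Let *a* be the shift in mean glucose caused by withholding metformin (in within-arm SDs) and *b* the change in delta z-score per SD of glucose. In a linear model with no unmodelled common cause:

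adjusted coefficient = total effect − *a* × *b*.

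The documents give neither *a* nor *b*. Taking 0.2 to 0.4 for each as assumptions, with a total effect of 0.41:

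| *a* (SD) | *b* (z per SD) | if withholding raises glucose | if it lowers glucose |
|---|---|---|---|
| 0 | any | 0.41 | 0.41 |
| 0.2 | 0.2 | 0.37 | 0.45 |
| 0.2 | 0.4 | 0.33 | 0.49 |
| 0.4 | 0.2 | 0.33 | 0.49 |
| 0.4 | 0.4 | 0.25 | 0.57 |

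**4. Power of the adjusted test, 95 per group.** With within-arm outcome SD 1, SE = √(1 − *b*²) × √(2/95) / √(1 − ρ²), where ρ² = (*a*²/4)/(1 + *a*²/4).

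- *a* = 0, *b* = 0.4: SE = 0.1330, coefficient 0.41, power 0.87. This is a genuine precision gain.
- *a* = 0.2, *b* = 0.2: SE = 0.1429, coefficient 0.37, power 0.74.
- *a* = 0.4, *b* = 0.4: SE = 0.1356, coefficient 0.25, power 0.45.

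**5. Common cause of glycaemia and growth outside the model.** Suppose glucose has no effect on growth (*b* = 0), but a third factor loads *u* on each. The adjusted coefficient is then 0.41 − *a* × *u*². Simulation with 1,000,000 records per scenario agrees: *a* = 0.2, *u* = 0.3 gives 0.39, and *a* = 0.5, *u* = 0.5 gives 0.29. The estimate moves although glucose plays no causal part. These loadings are also assumed.

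**The case against.** The strongest reply is that the trial's main analysis is untouched. The statistical methods section defines it, and the sample size section only describes a further adjusted analysis. This stands. A reader might infer that the primary result, or the difference for which the trial is powered, is compromised. The documents do not support that, because "linear regression models adjusted for baseline z-score and minimisation variables" contain no glucose term.

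A second reply is that the two sections need not conflict. A main model and an additional adjusted one can coexist, and the SAP is to confirm the adjustment set. This stands in part. The fault is not that two models exist. It is that the sample size section justifies its covariates by precision, does not label the analysis and does not relate it to the main model. The words as appropriate do not cure a rationale that holds only for pre-randomisation covariates.

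Third, the covariates might be meant as baseline values, which Table 1 shows are collected. That is possible, and it makes the fix easy. But the text does not say so, and the names match the outcomes defined across visits.

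Fourth, both arms are treated to the same glucose targets, so the between-arm difference may be small. This also stands: with no shift there is no bias, and precision improves. A reader might infer a large loss of effect from the upper ends of the assumed ranges, but nothing in the documents supports a particular size or even a direction. Still, the protocol plans to compare glucose between arms, so it does not assume equality.

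Finally, not every common cause is unmeasured. Missed doses are recorded at study visits, and weight and skinfolds are measured. They are simply not named as covariates of this model.

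**Conclusion.** The point holds in a limited form. As written, the adjusted analysis in the sample size section conditions on variables that the protocol itself treats as outcomes of treatment. It therefore estimates at best a direct effect not passing through glucose, and that only if the common causes of glycaemia and growth are accounted for. It should not be presented as a more precise estimate of the effect of withholding metformin. The intention-to-treat comparison in the statistical methods section and the sample size are unaffected.

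The conclusion about what is being estimated rests on the documents alone. The size does not. The figures of 0.37 to 0.25, or 0.45 to 0.57 in the other direction, illustrate a linear model with assumed shifts and slopes, and the bias is zero if glucose does not differ between arms.

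**What to change.** In the sample size section, and in the SAP if it repeats the wording:

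1. Remove mean daily glucose and time in target from the treatment-effect model, or restrict glycaemic adjustment to the baseline-visit summary in Table 1, collected before allocation. HbA1c at eligibility is a poorer substitute: it is only one of several routes to inclusion, and the article does not show that every woman has a value.
2. State that the adjusted model for the treatment effect is the one in the statistical methods section, with baseline z-score and minimisation variables. If a baseline glycaemic covariate is wanted, add it there explicitly.
3. Move any model that uses on-treatment glucose to the exploratory mechanism analyses under {20b}. Label it a mediation analysis and state its assumptions, including which common causes of glycaemia and growth are adjusted for.

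The cost is a sentence or two of text. No new data, visits or participants are needed. The change should be made before outcome data are examined by arm.
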